The primary hypothesis states that loneliness (3-Item UCLA Loneliness Scale) at admission, the change in loneliness from admission to discharge, and their interaction (admission x change in loneliness) will significantly predict depressive symptom severity, assessed using the Montgomery–Åsberg Depression Rating Scale (MADRS), in a linear mixed-effects model, tested using an omnibus likelihood ratio test (*α* = .05). As depression is our main outcome variable, we will also address this hypothesis for self-report data, measured with the Patient Health Questionnaire (PHQ-9). The loneliness scores of the 6-Item De Jong Gierveld Loneliness Scale will serve for sensitivity analysis to examine the measurement robustness and construct validity. A more detailed but exploratory analysis of the fixed and random effects and time-varying loneliness and depression within the inpatient and follow-up treatment period will be explored with linear mixed model analysis to 1) examine whether loneliness has a role in the inpatient therapy effect on depression symptom severity and its maintenance after discharge, 2) investigate the clinical relevance of chronic loneliness, and 3) describe the bidirectional relationship between loneliness and depression at all measures. To evaluate the prognostic value of baseline loneliness (3-Item UCLA Loneliness Scale) to predict response at discharge (≥ 50% reduction in MADRS) and the prognostic utility of loneliness at discharge to predict relapse (≥ 10 MADRS points more from discharge to follow-up or ≥ 22 MADRS points at follow-up), receiver operating characteristics (ROC) will be determined and reported in an exploratory fashion. Along with the main objective to investigate the clinical relevance of loneliness and depression, we will test several exploratory hypotheses. Since the duration of inpatient treatment has implications for the allocation of healthcare resources, we will test whether loneliness at admission and change in loneliness from admission to discharge are significant predictors of inpatient length of stay after adjusting for covariates. The secondary objective of the study is to identify the biopsychosocial processes that shape the interaction between loneliness and clinical depression. To this end, statistical analyses of additional clinically relevant outcomes (such as quality of life and suicidality) as well as interactional effects of potentially shared psychosocial mechanisms (including social support, social network, comorbidities, general health and physical activity) will be conducted. Exploratory analysis of blood, saliva and stool markers including metabolic, hormonal, immunological, and neurotrophic factors as well as microbiome diversity will deepen the understanding of pathophysiological processes. We hypothesize that more depressed and more lonely people will have the most unfavorable metabolic profile in blood markers (Low-Density-Lipoprotein, HbA1c), higher levels of inflammation or cellular stress (sphingolipid metabolism) and less neuroplasticity (BDNF). In terms of saliva pattern markers, we assume a higher stress response (cortisol, α-amylase activity) in individuals with more severe depression and loneliness. For stool markers, it is hypothesized that more depressed and lonely people have a less diverse stool microbiome (alpha-diversity). We hypothesize the changes in biomarker profile from baseline to discharge from clinic and baseline to follow-up to be associated with changes in depression severity and changes in loneliness experience.

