
As empirical assumptions for the interplay between depression and loneliness in the inpatient and follow-up depression therapy are rare, we decided to set a change of 2 points in the MADRS per 1 SD of loneliness (3-Item UCLA Loneliness Scale) as the minimum meaningful association that shall be detected via the interaction (baseline x change) over the inpatient and post-treatment course. The model tested baseline loneliness and change in loneliness with at least 1.75 points MADRS as we have no empirical assumptions about which association is more significant for this setting, but we have a theoretical assumption that these single associations are less significant than their interaction. An omnibus likelihood ratio test will evaluate these assumptions in a single model, followed by Holm-Bonferroni corrected single tests to evaluate these three assumptions. This step will also evaluate the direction of effects and theoretical plausibility (more loneliness at baseline and less change in loneliness shall predict higher depressive symptom severity). The primary analysis of the linear mixed model includes all three measurement points as a categorial factor. Potential time- effects will serve as covariates in this model and will be reported exploratory with no influence on sample size calculation. Studies examining the clinical course of inpatient depression treatment measured with the MADRS report partly comparable values of MADRS at baseline (≈ 30 points) (62–64) and discharge, though findings remain heterogeneous (65, 66). Model assumptions for this sample size calculation were therefore based on plausible clinical values: T0 = 30, T1 = 16, T2 = 15 MADRS points, with a constant standard deviation of *SD* = 8 across all time points. Between-person differences in depression symptom severity (MADRS) were considered with fixed and random slopes, and ICC was set at .50. Power simulation involved assumptions of approximately 5% missing completely at random (MCAR) and 10% missing at random dropout at T2 (MAR). Sample size estimation was performed with R using the following packages: lme4, lmerTest, MASS and tidyr. The simulation for the overall model yielded a statistical power of ≥ 80% for all three assumptions at *n* = 172 with 15% combined dropout rate (MCAR, MAR), resulting in a total of *n* = 199. The number of simulations was 500 (nsim = 500) at a significance level of *α* = 0.05 for the omnibus likelihood-ratio test, with Holm-Bonferroni corrected single hypothesis tests. As depression can lead to cognitive distortion, correlations between loneliness and depression might be dependent on the measurement point, and given the insufficient clinical validation of the loneliness measures, it remains unclear whether the assumptions of a normal distribution and the assumed level of measurement adequately describe the interplay between depression and loneliness. Additional statistical methods are employed in an explorative and descriptive manner (generalized linear mixed-effects model and mixed analysis of variance). Power-analysis for mixed ANOVA using G*Power Version 3.1.9.7, with categorical groups of ‘high’ and ‘low’ loneliness (median-split) when considering an α error of 0.05, a power of 0.9 (1-β error probability) and a correlation value among repeated measures of 0.5 for the group’s results an estimated sample size of *n* = 36 participants assuming a medium effect size (*f* = 0.25), and *n* = 214 participants assuming a small effect size (*f* = 0.10).

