### Statistical analysis

2.6

To perform the statistical analysis, IBM SPSS Statistics Version 29 (96) and R (97) are used. To address the primary objective of this study, which is to examine the clinical relevance of the interplay between loneliness and depression in an inpatient and post-inpatient treatment setting, a set of statistical approaches is employed. To address the primary hypothesis, a linear mixed model with likelihood ratio test will be conducted to test against the null hypothesis that baseline loneliness, change in loneliness or their interaction have no additional association with the symptom severity in the course of depression (T0, T1, T2). In the primary linear mixed-effects model, depressive symptom severity (MADRS) is modeled across the three main assessment points (T0 = admission, T1 = discharge, T2 = three-month follow-up), with time entered as a categorical factor. Baseline loneliness at T0 (applied to T0, T1, and T2), the change in loneliness from admission to discharge (applied to T1 and T2), and their interaction (baseline × change) are entered as fixed effects, alongside random intercepts and random slopes capturing individual differences in symptom level and course. Because the length of inpatient stay differs between participants, the individual inpatient treatment duration (days from admission to discharge) is included as a time-related covariate rather than assuming a fixed interval between T0 and T1. The biweekly interim assessments are not part of the primary model and are reserved for the exploratory within-/between-person trajectory analyses described below. The primary test is an omnibus likelihood-ratio test of the null hypothesis that baseline loneliness, change in loneliness, and their interaction jointly show no association with the course of depressive symptom severity; only if this omnibus test is significant are the three individual coefficients examined, with Holm–Bonferroni correction. The formal model specification and the complete list of covariates are provided in the **Supplementary Material** (Section 4 and **Supplementary Table S1**). All models will be controlled for time-effects (e.g., length of inpatient treatment duration), measures obtained at the same timepoint (e.g. explorative analysis of measurement specific associations of loneliness and depression), recruitment site, gender and age and will be tested for further covariates such as social anxiety and social support. The primary analysis sample will include all participants who completed T0 and T1 depression severity measures (MADRS) and loneliness measures (3-Item UCLA). For each questionnaire, missing individual data points are imputed using person-mean imputation, provided that no more than 20% of the data is missing. Participants with an inpatient stay shorter than seven days (post-enrollment exclusion criterion) are not part of the primary analysis set, since no discharge assessment (T1) is obtained for them; where baseline (T0) data are available, they are retained in the sensitivity analyses of all available data. The extent and pattern of missing values will be described for all inference statistical analysis. Given that dropout is likely associated not only with observed characteristics (MAR) but also with unobserved post-discharge symptom severity (MNAR), sensitivity analyses will include pattern-mixture models or selection models to evaluate the robustness of primary findings under MNAR assumptions. As a pragmatic benchmark, a worst-case analysis will be performed assuming that all dropouts at T2 experienced no improvement (last observation carried forward) or deterioration (fixed offset of +5 MADRS points).

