Secondary outcomes (quality of life, suicidality, social support and others) and biosamples will be analyzed exploratively and reported descriptively. To account for multiple testing in exploratory analysis, p-values will be adjusted using the Benjamini-Hochberg false discovery rate (FDR) procedure. To evaluate prognostic sensitivity and specificity of loneliness measures loneliness at the beginning of inpatient treatment and at discharge, cutoff values for loneliness scores (with 3-Item UCLA and 6-Item DJGLS Loneliness Scales being considered separately) are assessed exploratory by using ROC analysis. The severity of depression symptoms serves as reference standard for predicting response, which is defined as ≥ 50% reduction in MADRS scores from baseline (T0) to discharge (T1), and depression symptom severity measured with MADRS at T2 serves as reference standard for predicting relapse (defined as one or both of the following conditions: ≥ 10 MADRS points more from discharge to follow-up or ≥ 22 MADRS points at follow-up measurement), respectively. The exploratory ROC results are strongly sample-dependent. Because the cutoff values are derived from the present sample, their predictive value and transferability are markedly limited; the ROC analysis should therefore be regarded only as a first attempt at course- and risk-stratification, the validity of which would need to be confirmed in independent samples. A detailed descriptive presentation of all the measurement time points and all variables assessed will be performed, as well as an exploratory analysis using (generalized) linear mixed models.

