
Given that the study design does not permit definitive causal conclusions to be determined about the direction of all fixed and random effects, the findings are still expected to provide valuable insights and relevant implications. In particular, the following insights can be obtained (1): a report on whether patients with different levels of loneliness receive equal benefits from inpatient multimodal depression treatment; (2) insights into changes in loneliness during and after depression treatment; (3) important preliminary findings regarding the shared and distinct biopsychosocial mechanisms underlying loneliness and depression; and (4) the relationship of loneliness and depression on to secondary outcomes, including quality of life and suicidality.

Should the primary hypotheses be confirmed — that is, if baseline loneliness, change in loneliness or their interaction is significantly associated with the level of depressive symptom severity across the treatment course — this may carry implications for clinical practice. First, a brief loneliness screening (requiring less than two minutes using the 3-Item UCLA Loneliness Scale) might be considered for integration into routine psychiatric admission assessments, as it may enable clinicians to identify patients at risk for poorer treatment outcomes early in the treatment process — though randomized controlled studies would be needed to determine whether such screening translates into improved clinical outcomes. Second, the exploratory distinction between more situational and more enduring aspects — examined here only descriptively and without a validated state-trait measure — may, if associated with the course of depressive symptom severity, generate hypotheses for future interventional studies. Such studies could evaluate whether loneliness-focused components (e.g., cognitive restructuring of maladaptive social cognitions or facilitated social re-engagement during the transition from inpatient to outpatient care) add value to multimodal depression treatment. Any inference about modifiability would require an interventional design and lies beyond the scope of the present observational study. Third, the finding that loneliness at discharge predicts relapse would underscore the importance of addressing social connectedness as part of discharge planning and aftercare, a dimension that is currently underrepresented in German psychiatric treatment guidelines.

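### The exploratory relapse ROC uses discharge loneliness alone, so it cannot separate a predictor of relapse from a marker of residual depression, yet an aftercare implication is drawn from it

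*Protocol article*

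**What the plan says.** The Introduction of the protocol article plans to examine "the prognostic utility of loneliness at discharge to predict relapse" by ROC, on an exploratory basis. Section 2.6 (Statistical analysis) gives the method: "cutoff values for loneliness scores (with 3-Item UCLA and 6-Item DJGLS Loneliness Scales being considered separately) are assessed exploratory by using ROC analysis". No other predictor is named, either as a comparator or jointly with loneliness.

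For the outcome, "depression symptom severity measured with MADRS at T2 serves as reference standard for predicting relapse", and relapse is "defined as one or both of the following conditions: ≥ 10 MADRS points more from discharge to follow-up or ≥ 22 MADRS points" at follow-up. Either condition is enough. Neither section requires response or remission at discharge first, so a patient at 22 or more at both discharge and follow-up is counted as relapsed.

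Section 2.6 also states, for the regression analyses: "All models will be controlled for time-effects (e.g., length of inpatient treatment duration), measures obtained at the same timepoint". The ROC paragraph does not take this up.

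The Discussion lists three clinical implications. The first carries the reservation that randomized studies would be needed, and the second is limited to generating hypotheses. The third reads "the finding that loneliness at discharge predicts relapse would underscore the importance of addressing social connectedness as part of discharge planning and aftercare" and has no reservation of its own.

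**The concern.** The aftercare implication needs loneliness to say something about relapse that the MADRS from the same visit does not already say. A ROC of one score answers a different question: whether patients labelled as relapsed had higher loneliness scores at discharge, for whatever reason.

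The two questions can have different answers. Patients discharged while still depressed tend to report more loneliness, and they are also more likely to be at 22 or more three months later. An AUC above 0.5 can then arise although loneliness has no link of its own with the later course. The label adds to this because it counts persistent depression as relapse.

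At stake is the reading of an exploratory result: a recommendation on social connectedness at discharge could rest on what is only residual symptom severity. The primary mixed-model test is not affected.

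**Working it through.** The article gives no relapse rate, AUC or power for this ROC, so there is no stated figure to reproduce. The check asks what the planned ROC would show if loneliness added nothing.

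**Inputs from section 2.3**
- MADRS means: "T0 = 30, T1 = 16, T2 = 15 MADRS points". SD: "8 across all time points".
- ICC 0.50, read here as the discharge-to-follow-up correlation ρ. This is an assumption; range 0.3–0.7.
- Same-visit correlation r between loneliness and depression of 0.50. The article cites it from non-clinical data, so it is also an assumption; 0.3 was tried as well.
- Analysable n = 172.

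**Step 1: what the label captures (ρ = 0.5, normal scores)**
- Level criterion: P(T2 ≥ 22) = P(Z ≥ (22 − 15)/8) = P(Z ≥ 0.875) = 19.1%.
- Rise criterion: the change has mean 15 − 16 = −1 and SD 8·√(2(1 − 0.5)) = 8, so P(change ≥ 10) = P(Z ≥ 11/8) = P(Z ≥ 1.375) = 8.5%.
- Either criterion, by simulation: about 23%. Of these cases about 82% meet the level criterion, 64% meet it alone and 18% meet the rise criterion alone. About 40% were already at 22 or more at discharge, and about 21% were no worse than at discharge.
- With scores rounded to whole numbers the picture is the same: about 25% relapse, 84% of them on level, 42% already at 22 or more at discharge.

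**Step 2: why the two criteria pull in opposite directions**

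If loneliness depends only on discharge MADRS, then:
- corr(loneliness, T2 MADRS) = r·ρ = 0.5 × 0.5 = +0.25
- corr(loneliness, change) = −r·√((1 − ρ)/2) = −0.5 × √0.25 = −0.25

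The level criterion alone therefore gives an AUC of about 0.63 and the rise criterion alone about 0.36. The combined label is an offset between them, weighted towards the level.

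**Step 3: the ROC when loneliness adds nothing (r = 0.5, n = 172, Mann–Whitney test of AUC = 0.5)**

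| ρ | Relapse | Level-only share | Already ≥ 22 at discharge | AUC of loneliness | p<0.05 |
|---|---|---|---|---|---|
| 0.3 | 25% | 50% | 29% | 0.50 | about 6% |
| 0.5 | 23% | 64% | 40% | 0.56 | about 20% |
| 0.7 | 21% | 82% | 56% | 0.64 | about 69% |

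Runs with rounded scores, and with loneliness cut to the 3–9 scale (mean 6, SD 1.8 assumed), put these shares at about 5%, 20–25% and 70–75%. With r = 0.3 and ρ = 0.5 the AUC is 0.53 and about 10% of studies reach p<0.05.

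**Step 4: the same data with discharge MADRS in the model (r = 0.5, ρ = 0.5)**

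A logistic model with discharge MADRS (linear plus quadratic) has an AUC of 0.68. Adding loneliness leaves it at 0.68, an increment of 0.00. The adjusted test of loneliness rejects in about 5–6% of studies, and stays near 5% at ρ = 0.3 and 0.7.

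**Step 5: a harder case**

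Suppose loneliness marks a patient's stable severity rather than the discharge score, so that it correlates equally with MADRS at both visits. With r from 0.3 to 0.5 its AUC is 0.61–0.69 and 55–95% of studies reach p<0.05. Adjusting for one discharge MADRS still leaves 34–85%.

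**The case against.** The strongest defence is that the ROC is declared exploratory and sample-dependent, with external validation required before clinical use, and that a single-marker ROC is a legitimate description of how a brief screen classifies patients. No test of AUC = 0.5 is stated, and exploratory p-values are to be adjusted by Benjamini–Hochberg, so the rejection rates above are a yardstick and not the plan's procedure. The Discussion also concedes that severe depression can colour loneliness ratings and that the two constructs may not be well separated. Other exploratory mixed models will look at the course after discharge. All of this stands, and it keeps the point to one of interpretation.

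It does not answer the point. None of the caveats promises a comparison with discharge severity. Validation in a new sample, FDR adjustment and split-sample checks would all reproduce the same confounding. The control described for the models does not reach a cutoff analysis of a raw score. The paragraph holding the aftercare statement is conditional on the primary hypotheses being confirmed, but relapse is not part of them. The implication is worded conditionally, yet its condition is only that loneliness predicts relapse, which a marginal ROC could appear to show.

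A reader might infer two stronger things that the documents do not support. One is that discharge MADRS is not used at all: it is part of the label through the 10-point rise, and that criterion partly cancels the artefact. The other is that the ROC will find loneliness predictive: at the plan's own values roughly four studies in five would not show it if loneliness added nothing. Much higher rates arise if the 22-point level is taken as the only criterion, but that is not the plan's definition.

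**Conclusion.** The point holds as a limit on interpretation. The relapse ROC, as described, cannot distinguish loneliness as a predictor of relapse from loneliness as a marker of residual depression, and the aftercare implication goes further than it can support.

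The size is moderate and depends on assumptions. At the central values a loneliness score with no added value looks predictive in about one study in five to one in four, against about one in twenty when discharge MADRS is in the model. The excess vanishes if MADRS tracks weakly from discharge to follow-up and is large if it tracks strongly. The result rests on reading the ICC as the discharge-to-follow-up correlation, on a correlation from non-clinical data that the article itself calls hardly comparable, and on normal scores. That the label is mainly a level criterion is firmer: level-only cases make up 50–82% of relapses over the whole range tried.

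**What to change.** - Keep the single-marker ROC as description.
- In section 2.6, add a logistic model for relapse with discharge MADRS, allowing non-linearity because the label combines a rise and a level, and then add discharge loneliness. Report the AUC of discharge MADRS alone, the AUC increment with a confidence interval, and the likelihood-ratio test.
- Report how many relapse cases are level-only, how many are change-only, and how many were already at 22 or more at discharge. This changes no threshold. It shows how far the label reflects persistence rather than worsening.
- In the Discussion, make the aftercare statement conditional on the increment, and note that one discharge MADRS may not fully remove confounding by stable severity.

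The cost is one more exploratory model on data already collected, plus wording. The downside is that the predictive value of loneliness will usually look smaller.
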